## Abstract

**Background:**

Previous studies of acupuncture show favourable results for both subjective and objective outcomes of dry eye. However, firm conclusions could not be drawn from these studies because the quality of the trials was too low to establish concrete evidence. Therefore, this study was designed both to avoid the flaws of the existing trials and to assess the effectiveness, cost-effectiveness and qualitative characteristics of acupuncture treatment for dry eye.

**Methods/design:**

One hundred fifty participants with dry eye will be recruited into three independent hospitals from different areas: Korea Institute of Oriental Medicine, DongGuk University Ilsan Oriental Hospital and Dongshin University Gwangju Oriental Hospital. The number of participants required was calculated from the data of a previous, relevant study. These patients will be randomly allocated into acupuncture treatment or artificial tear groups. Either 17 acupuncture points (bilateral BL2, GB14, TE 23, Ex1, ST1, GB20, LI4, LI11 and single GV23) will be used 3 times a week or disposable artificial tear drops (Refresh Plus^®^, ALLERGAN) will be provided for use at least once a day for 4 weeks. The ocular surface disease index (OSDI), tear film break-up time (TFBUT), Schirmer I test, visual analogue scale (VAS) for self-assessment of ocular discomfort, general assessment (by both acupuncture practitioners and participants) and quality of life (QOL) through the Measure Yourself Medical Outcome Profile-2 (MYMOP-2) will be assessed for approximately 3-months for each study participant. In addition, qualitative study and cost-effectiveness of acupuncture treatment will be conducted.

**Trial registration:**

ClinicalTrials.gov (Identifier: NCT01105221).

## Background

Dry eye is not a life-threatening disease, but it is one of the most common and irritating conditions in ophthalmology. Because of recent data on both the pathological mechanism and aetiology, the definition of dry eye has been changed from simple ocular discomfort (related to the deficiency or hyper-evaporation of tears) to a multifactorial disease (with ocular discomfort and visual disturbances, which are related to tear-film instability and both the hyper-osmolarity and chronic inflammation of the ocular surface) [1]. The overall prevalence has been reported to be between 5 and 35 percent in different populations [2]. The incidence is now increasing more rapidly than other ophthalmologic diseases such as cataracts, retinal disease and glaucoma [3]. This may be related to an increase in average life expectancies, environmental pollution, and adverse events of various ophthalmologic interventions including LASIK surgeries and medications (including antihistamines, which serve as a major risk factor for dry eye) [2].

Acupuncture is a widely used treatment modality for various conditions, including ophthalmologic diseases [4]. It is generally accepted as an effective treatment option in clinical practices. However, neither its efficacy nor its safety is well established. This is primarily because the quality of the clinical trials that assess acupuncture is too low to draw definitive conclusions. Well-designed, rigorous research is needed to establish the evidence for wider usage of acupuncture, including for the treatment of dry eye [5].

In acupuncture research, selecting an appropriate control (including sham acupuncture) is a significant challenge to overcome. Several types of sham acupuncture methods have been developed, but it is not easy to maintain effective masking for participants when using these modalities. It is also difficult to exert a placebo effect that is distinct from real (verum) acupuncture [6]. In addition, a recent review about acupuncture research reported that sham acupuncture has a tendency to show equivalent efficacy compared to verum acupuncture [7]. Therefore, it may be easy to draw a hasty conclusion (i.e. that acupuncture has either only a small or no specific effect) in sham-controlled clinical trial designs. Comparative-effectiveness studies using either usual care or standard treatment groups has its own value because it reflects real-world clinical conditions rather than research conducted under more ideal experimental conditions [8,9].

When we consider acupuncture as an effective intervention for dry eye, it becomes important to question both what components would be relevant for evaluating therapeutic effects and what benefits would be gained from treatment [10]. Recent research on complementary and alternative medicine examines effectiveness by using mixed-method approaches to show both the qualitative factors and the economic values of the interventions [8,11].

With this in mind, we designed a multicentre, randomised, controlled trial that compares acupuncture treatment with an artificial tear drop treatment (as an active control). We also added mixed-method analyses for both the cost-effectiveness and the qualitative study for a mixed method approach.

### Study aims

The primary aim of this study is to determine the effectiveness of acupuncture treatment for dry eye. The null hypothesis is that changes in the ocular surface disease index (OSDI) are equal in both the acupuncture treatment group and the artificial tear drop group after 4 weeks of treatment.

## Methods/Design

This study is a randomised, active-intervention controlled (using artificial tear drops), multicentre trial. Three clinical research centres in Korea will participate in this trial: Korea Institute of Oriental Medicine (Daejeon University Hospital), DongGuk University Ilsan Oriental Hospital and Dongshin University Gwangju Oriental Hospital. Eligible participants will be randomly allocated into either of the two groups (acupuncture or artificial tear drop) and will receive treatment for 4 weeks. Ophthalmologic tests and questionnaires for both ocular symptoms and quality of life will be assessed for up to 13 weeks after the first visit (Figure 1). Additional studies will proceed with the main outcome analyses (cost-effectiveness and qualitative factors).

**Figure 1 F1:**
[figure not shown]
**Study Flow Chart**.

### Eligibility Criteria

We will include patients who have dry eye symptoms (e.g. ocular itching, foreign body sensation, burning, pain and dryness, visual disturbance, ocular redness and sensation of tearing in a single eye or in both eyes) of at least moderate severity (i.e. tear film break-up time [TFBUT] is below 10 seconds and Schirmer I test result is below 10 mm/5 minutes) [12]. Participants will be excluded if they have prominent pathological changes of the eyelid, eyelashes, eyeball or eye accessories due to acute infection; Stevens-Johnson syndrome; Vitamin A deficiency; external injuries; a history of surgical operation related to the eye in the previous three months; punctual occlusion; sequelae of facial palsy; usage of anti-inflammatory eye drops within two weeks before entry; pregnancy; or usage of herbal medicine, acupuncture, or cupping therapy within 1 month before entry. In addition, usage of contact lenses within 2 weeks before entry, and throughout the study, is prohibited. The eligibility were assessed by physicians and ophthalmologists [13].

### Sample size

The results from a previous study were used to calculate the sample size [13]. The mean difference and standard deviation (SD) of OSDI after acupuncture treatment were 17.61 and 15.61, respectively. According to another clinical trial with artificial tear drop, the supposed mean and SD of the artificial tear group were 11.3 and 6.3, respectively [14]. A two-sided 5% significance level and 80% power were considered, and the following equation was used:

$$n=\frac{2\times {\left(z_{\alpha /2}+z_{\beta }\right)}^{2}\times \sigma^{2}}{\delta^{2}}$$

*z*_*α*/2 _= *z*_0.025 _= 1.96; *z*_1-*β *_= *z*_0.8 _= 0.84

Approximately 60 participants in each group were calculated to be required. Therefore, estimating a 20% dropout rate, 75 participants will be recruited into each group. Among the 3 participating centres, all located in Korea, approximately 50 participants will be assigned to each to ensure an even distribution.

### Randomisation and Allocation Concealment

Random numbers will be generated by a computerised random-number generator through the block-randomisation method of the SAS package (Version 9.1.3; SAS institute Inc.) for sequence generation. A clinical research associate (CRA) will make opaque blinded assignment envelopes (with consecutive numbers) and deliver them to each participating centre. The block size and treatment-assignment table will not be available to the researchers until the end of the study.

Random allocation will be performed at the second visit for each participant. According to the number assigned to a participant, the corresponding envelope will be opened in front of the participant to reveal treatment. Either acupuncture or artificial tear drop treatments will be initiated at the second visit after the assignment. Objective outcomes (i.e. Schimer test and TFBUT) will be examined by different ophthalmologists, while self-reported outcomes (e.g. OSDI, visual analogue scale (VAS), quality of life (QOL), and general assessment) will be assessed by different outcome assessors.

### Intervention

#### Acupuncture treatment

Certified acupuncture practitioners who have a minimum of 7 years of training and 3 years of clinical experience will perform the acupuncture treatments. They will take a one-day training course for this trial. This course will cover the study protocol, techniques for acupuncture treatment, the recording method for the clinical record form (CRF), and basic information about clinical research, a researcher's duty and research monitoring. The relationship between patients and practitioners can be an important factor when assessing the outcomes of acupuncture research [15]. Therefore, interactions between acupuncture practitioners and participants will be strictly limited, except when reporting adverse events.

Based on a literature review and a textbook about acupuncture for ophthalmologic diseases or dry eye [16], acupuncture points were chosen by an expert committee comprised of professors and researchers that specialise in acupuncture and ophthalmology of traditional Korean medicine. Seventeen acupuncture points (bilateral BL2, GB14, TE 23, Ex1, ST1, GB20, LI4, and LI11 and single GV23) will be located according to the WHO Standard Acupuncture Point Locations in the Western Pacific Region [17]. These will then be treated with 0.20*30 mm disposable acupuncture needles (Dongbang Co., Korea). The '*deqi*' sensation will be induced by twisting acupuncture and needles will be retained for 20 minutes before removal. Participants will have acupuncture treatments three times per week for four weeks.

#### Active comparator group using artificial tear drops

Artificial tear is one of the first choices in treatment for dry eye. Because the strategy for treating dry eye is to ease ocular discomfort and to improve quality of life, and to recover the ocular surface from chronic inflammation and tear film instability [18], artificial tear can be recommended as an active treatment. According to a survey report of ophthalmologists, preservative-free artificial tear was the most frequently selected medication for moderate to severe dry eye patients among various treatment modalities in Korea [19]. In this context, we chose preservative-free artificial tear as an active comparator intervention in this trial.

Participants allocated to this group will be offered preservative-free and one-day-use artificial tear drops (Refresh Plus^®^, ALLERGAN) and then educated on how to use them. According to the participants' discomfort from dry eye symptoms, it is recommended that the tear drops can be used at least once a day for four weeks. A diary of both the frequency and quantity of drops used will be collected at every visit.

In both groups, other treatments for dry eye will be forbidden during the study period. These other treatments include different types of artificial tear drops, drugs, supplements (e.g. cyclosporine, corticosteroids, biological tear substitute, and oestrogen), and alternative treatments (e.g. herbal medicine, acupuncture, and cupping therapy). However, participants will be allowed to use any kind of treatment for dry eye during the follow-up period. The usage of these treatments will be reported during the follow-up period.

### Primary outcome measurement

The OSDI is a questionnaire that consists of twelve questions about ocular irritation and the effect of dry eye on vision [20]. It will be assessed at the first, third, fifth, ninth and thirteenth week. For every question, participants will provide a score between zero and four, where zero equals "none of the time" and four equals "all of the time". OSDI scores will be calculated according to the following formula: OSDI = [(sum of scores for all questions answered)*100]/[(total number of questions answered)*4]. The Korean version of OSDI has not been validated yet. However, there is no available tool for evaluating dry eye that validation test for translation was finished about in Korea. So we will use the Korean version of OSDI which has been widely used for practice and research since 2006, in spite of these limitations [13,21,22].

### Secondary outcome measurement

A VAS for self assessment of ocular discomfort will be reported by participants. Ocular symptoms related to dry eye (e.g. ocular itching, foreign body sensation, burning, pain and dryness, blurred vision, sensation of photophobia, ocular redness, and sensations of tearing) will all be reported using a standard 100-mm VAS scale.

QOL questionnaire of the Measure Yourself Medical Outcome Profile-2 (MYMOP-2) will be used to assess dry-eye-related QOL [23,24]. A seven-point Likert scale (from zero-'Excellent' to six-'Worst') will be used. The questionnaire is: "During last week, how would you express your quality of life related to dry eye overall?" The VAS and questionnaire for QOL will be assessed at the first, third, fifth, ninth and thirteenth week.

The Schirmer I test (with anaesthesia) is a diagnostic method to measure the basic quantity of tear secretion [25]. After application of local anaesthesia, Schirmer test paper (Color BarTM Eagle Vision, USA) will be placed in the lateral third of the lower eyelid for five minutes while the participants' eyes are closed.

Tear film break-up time (TFBUT) is a method for observing tear film stability [26,27]. Sodium fluorescein (2.5%) will be applied to both eyes, and the tear break-up time (i.e. the interval between the last complete blink and the first appearance of a dry spot or disruption in the tear film) will be measured. Both the Schimer test and TFBUT will be assessed at the first, fifth and thirteenth week.

Acupuncture practitioners and participants will evaluate general improvement of dry eye-related symptoms using a five-grade scale: excellent, good, fair, poor and aggravation. This will be assessed after the end of the treatment period (the fifth week).

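### The practitioner-rated half of the general-improvement outcome is scored by those who deliver one of the two treatments, with no stated basis for rating the tear-drop arm, so it cannot support an unbiased between-arm comparison

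*Protocol article*

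**What the plan says.** The section on secondary outcomes defines the measure and its raters: "Acupuncture practitioners and participants will evaluate general improvement of dry eye-related symptoms using a five-grade scale", with grades from excellent down to aggravation. It is collected once, in the fifth week, after treatment has ended. The Abstract agrees on the raters: "general assessment (by both acupuncture practitioners and participants").

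The Acupuncture treatment section says who these practitioners are: "Certified acupuncture practitioners who have a minimum of 7 years of training and 3 years of clinical experience will perform the acupuncture treatments". It schedules three sessions a week for four weeks. Because the patient-practitioner relationship can influence outcomes, it adds that "interactions between acupuncture practitioners and participants will be strictly limited, except when reporting adverse events".

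The comparator section describes the other arm without mentioning an acupuncture practitioner: "Participants allocated to this group will be offered preservative-free and one-day-use artificial tear drops". Those participants are also taught how to use the drops, and they keep a diary of use.

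Randomisation and Allocation Concealment sets a rule for who takes the outcomes. Ophthalmologists other than the treating staff handle the objective tests, "while self-reported outcomes (e.g. OSDI, visual analogue scale (VAS), quality of life (QOL), and general assessment) will be assessed by different outcome assessors".

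**The concern.** A global improvement grade running from excellent to aggravation is a judgement, and a rater who knows the treatment can shift it without intending to. Here one of the two raters belongs to the group that delivers one of the two treatments. That rater is necessarily unmasked for the participants they needle and has a professional stake in the result.

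The arms also differ in what the rater can know. In one arm the practitioner group has repeated scheduled contact with the participant; in the other the article gives it no part in treatment. The two sets of grades would not measure the same thing, even if every rater were scrupulous.

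At stake is whether the practitioner grade can be read as evidence of a treatment difference. If it were set beside the tear-drop arm in the results, part or all of any gap could come from who did the rating and how well they knew the participant.

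**Working it through.** The point rests on no figure in the document, so the check sets the sections side by side.

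1. **Who rates.** The Abstract and Secondary outcome measurement both name acupuncture practitioners as well as participants. Because the two places agree, the practitioner rating is intended and is not a slip of wording.

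2. **Who the practitioners are.** The Acupuncture treatment section uses the same term for those who perform the acupuncture. The article defines no second, non-treating group under that name. That each rater is the participant's own practitioner is an inference; the article does not say so.

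3. **Masking in the acupuncture arm.** Someone who needles a participant knows the allocation, so a grade from the treating practitioner cannot be masked.

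4. **Contact by arm.**
   - Acupuncture arm: 3 sessions a week × 4 weeks = 12 scheduled sessions with the practitioner group.
   - Tear-drop arm: no scheduled treatment contact with the practitioner group is stated. The Adverse events section mentions practitioners as possible examiners of unexpected responses in a passage covering both treatments, but that is not a treatment role and gives no stated basis for grading improvement.

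5. **How many practitioner ratings there would be.** The planned recruitment is 75 per group. If only the acupuncture arm is rated, there are at most 75 ratings. If both arms are rated, there are at most 75 + 75 = 150. The article does not say which applies. In the first case there is nothing to compare; in the second the comparison rests on unequal knowledge and an interested rater.

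6. **Fit with the assessor rule.** Randomisation and Allocation Concealment lists general assessment as self-reported and gives it to different outcome assessors. A practitioner's grade is not self-reported, so there are two possible readings:
   - The rule covers the whole general assessment, and then the secondary-outcome section conflicts with it.
   - The rule covers only the participant's grade, and then there is no conflict, but no stated assessor safeguard applies to the practitioner's grade.

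   The weakness in the practitioner grade remains under either reading.

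7. **Where the outcome is analysed.** The Statistical analysis section names OSDI, TFBUT, Schirmer, QOL and VAS for ANCOVA. General assessment is not in that list.

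**The case against.** The strongest reply is that the stated plan makes no between-arm test of this grade. General assessment is missing from the ANCOVA list, and how it is summarised may be left to a fuller protocol or analysis plan that is not shown. **This stands.** A reader might infer that the practitioner grade is formally compared between arms, but the article does not say so. It is collected as a named secondary outcome in a two-arm trial and is therefore open to comparison; no more than that can be claimed.

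The second reply is that there is no contradiction over assessors, because the rule is limited to self-reported outcomes and the article consistently describes two separate grades. **This is a fair reading and cannot be excluded.** A reader might call the practitioner rating a breach of the separate-assessor rule; the text supports only that the two sections sit uneasily together.

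Third, the limit on interaction does not forbid a week-5 rating. **This also stands.** It would be tempting to say that the practitioner has no legitimate basis for grading, but 12 scheduled sessions give an obvious basis in the acupuncture arm. The gap is in the tear-drop arm.

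Fourth, the trial is openly comparative, and participants are unmasked too, since the envelope is opened in front of them. That is true, and it is not the complaint here. The participant's grade is at least defined in the same way in both arms; the practitioner's is not.

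Last, who rates the tear-drop arm is a logistical detail that a condensed article may omit. That is reasonable taken alone. It does not change what the article does state: that the people delivering one treatment are outcome raters.

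**Conclusion.** The point holds for the practitioner-rated half of one secondary outcome, measured once. As written, that half comes from unmasked raters with an interest in one arm, and on an unequal or unstated basis across arms. It does not support an unbiased between-arm comparison.

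The size cannot be derived from the document. Bias towards acupuncture is what one would expect, but the text does not demonstrate it. A reader might go further and take the bias as certain in direction, or as affecting all 150 participants. The article supports neither: it gives no evidence on direction and does not establish that tear-drop participants receive a practitioner grade at all.

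The conclusion assumes that the practitioners who rate are drawn from those who treat, which rests on the shared term. The participant's grade, the primary OSDI comparison, the sample size and the outcomes named for ANCOVA are untouched by this defect. It is worth correcting, but it does not threaten the trial's main conclusion.

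**What to change.** **Preferred change.** Have the outcome assessors already named under Randomisation and Allocation Concealment make the observer's general-improvement rating in both arms, in the fifth week, without being told the allocation. Keep the participant rating as it is. The article calls these assessors different but does not say that they are masked, so the wording should add this.

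**Alternative.** If the practitioner rating is kept, report it descriptively within the acupuncture arm only, and state that no between-group comparison will be made.

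In either case, align the Abstract, Randomisation and Allocation Concealment, and Secondary outcome measurement, so that each says who gives which rating and in which arm.

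**Cost.** This needs changes to protocol and case record form wording, and it uses assessors already in the trial. The between-group practitioner score is lost, but it could not have been interpreted with confidence. Masking of the assessors may be imperfect, because participants know their treatment and may disclose it. The change should be made before fifth-week data are collected, since a rating by the wrong person cannot be repaired afterwards.
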